# DiaSurg 2 trial - surgical *vs*. medical treatment of insulin-dependent type 2 diabetes mellitus in patients with a body mass index between 26 and 35 kg/m^2^: study protocol of a randomized controlled multicenter trial - DRKS00004550

**DOI:** 10.1186/1745-6215-14-183

**Published:** 2013-06-20

## Abstract

**Background:**

Type 2 diabetes mellitus (T2DM) is a disease with high prevalence, associated with severe co-morbidities as well as being a huge burden on public health. It is known that glycemic control decreases long-term morbidity and mortality. The current standard therapy for T2DM is medical treatment. Several randomized controlled trials (RCTs) performed in obese patients showed remission of T2DM after bariatric surgery. Recent RCTs have shown bariatric procedures to produce a similar effect in non-morbidly and non-severely obese, insulin-dependent T2DM patients suggesting procedures currently used in bariatric surgery as new therapeutical approach in patients with T2DM. This study aims at investigating whether Roux-en-Y gastric bypass (RYGB) is an efficient treatment for non-severely obese T2DM patients in terms of preventing long-term complications and mortality.

**Methods:**

The DiaSurg 2 trial is a multicenter, open randomized controlled trial comparing RYGB including standardized medical treatment if needed to exclusive standardized medical treatment of T2DM (control group). The primary endpoint is a composite time-to-event endpoint (cardiovascular death, myocardial infarction, coronary bypass, percutaneous coronary intervention, non-fatal stroke, amputation, surgery for peripheral atherosclerotic artery disease), with a follow-up period of 8 years. Insulin-dependent T2DM patients aged between 30 and 65 years will be included and randomly assigned to one of the two groups. The experimental group will receive RYGB and, if needed, standardized medical care, whereas the control group will receive exclusive standardized medical care, both according to the national treatment guidelines for T2DM. Statistical analysis is based on Cox proportional hazards regression for the intention-to-treat population. Assuming a loss to follow-up rate of 20%, 200 patients will be randomly allocated to the comparison groups. A total sample size of *n* = 400 is sufficient to ensure 80% power in a two-tailed significance test at alpha = 5%.

**Discussion:**

The DiaSurg2 trial will yield long-term data (8 years) on diabetes-associated morbidity and mortality in patients with insulin-dependent T2DM receiving either RYGB or standardized medical care.

**Trial registration:**

The trial protocol has been registered in the German Clinical Trials Register DRKS00004550.

## Background

### Rationale of the trial

According to WHO data, in 2000 the worldwide prevalence of type 2 diabetes mellitus (T2DM) was 2.8%, and in 2030 it is expected to rise to 4.4% [1,2]. Approximately 6 million people in Germany are currently suffering from T2DM, among whom 2 million are insulin-dependent [3,4]. A high proportion of these patients already suffer from T2DM-related diseases, such as micro- and/or macrovascular diseases resulting in neuro-, nephro-, retinopathy, myocardial infarction, and stroke [5,6]. The treatment of these co-morbidities renders T2DM one of the most expensive diseases in terms of public health expenditure in Germany [7]. Current guidelines recommend medical therapy for the treatment of T2DM as the gold standard [8,9]. It is known that sufficient glycemic control, defined by the German Diabetes Association and International Diabetes Foundation as HbA1c <6.5%, decreases long-term morbidity [6,8-10]. Current guidelines with the aim of lowering HbA1c-levels are therefore being reconsidered, owing to the growing number of studies showing an increased mortality rate for patients with lower HbA1c [11-14].

Obesity is considered a risk factor for the development of T2DM [15]. For patients with class 2 obesity (BMI >35 kg/m^2^) with co-morbidities and patients with class 3 obesity (BMI >40 kg/m^2^), bariatric surgery is recommended when conservative attempts do not result in substantial weight loss [16]. Existing evidence reports that bariatric surgery not only leads to substantial weight loss, but also to T2DM remission in 42% to 78% of the patients who have undergone RYGB [17-19]. In addition, T2DM-related diseases, such as cardiovascular diseases, nephropathy, retinopathy, neuropathy, hyperlipidemia, and hypertension, are supposed to be avoided or at least delayed in their progress after metabolic surgery [19-21]. In the Swedish Obese Subjects (SOS)-Study 35% of T2DM patients and 19% of patients suffering from preoperative hypertension were still in remission 10 years after surgery [22]. The beneficial effects of bariatric surgery on T2DM appeared shortly after surgery, and before major weight loss, leading to the hypothesis that weight loss alone is not solely responsible for T2DM remission. In an experimental study, Rubino *et al.* were able to prove that these effects are not dependent on weight loss alone [23]. These findings led surgeons to perform bariatric procedures on non-severely obese patients (overweight and obesity class 1; BMI 25–35 kg/m^2^) suffering from T2DM [21,24-26]. A recent randomized controlled, single-center trial in patients with a BMI of 25–35 kg/m^2^ showed T2DM remission in 93% of patients following Roux-en-Y gastric bypass (RYGB) and 47% of patients following laparoscopic gastric sleeve resection [27]. The effect of T2DM remission could therefore also be shown in non-severely obese patients.

This randomized controlled multicenter trial assesses whether bariatric surgery can be used as an alternative in the primary care of T2DM, potentially leading to fewer strokes or cardiovascular death and thus preventing long-term morbidity and mortality well-known in T2DM patients.

### Objective

The aim of DiaSurg 2 is to investigate the time-to-event of T2DM-induced morbidity and mortality after RYGB compared to medical treatment according to the most current clinical guidelines in patients with insulin-dependent T2DM.

## Methods/design

### Trial design

Diasurg 2 trial is a multicenter, open randomized controlled trial. Patients of the experimental group receive RYGB surgery and standardized medical treatment if needed. Patients in the control group receive exclusive standardized medical treatment of T2DM.

### Sample size

Two hundred patients per group (including the expected dropouts) will be randomized for this trial, accounting for a total of 400 patients.

### Patient selection criteria

Eligible patients need to have a diagnosis of insulin-dependent T2DM going back at least 3 months. Furthermore, they should have proof of at least one microvascular manifestation of T2DM (for example, nephropathy, retinopathy, neuropathy) and have sufficient residual endocrine pancreatic function, which is the premise for autogenic glycemic control. Residual endocrine pancreatic function is assessed by glucagon-stimulated fasting C-peptide laboratory tests with a minimum of 1.5 ng/mL. Eligible participants must have a body mass index (BMI) between 26 and 35 kg/m^2^, be aged between 30 and 65 years and be able to provide informed consent. Negative islet cell autoantibody testing will be required for patients who started insulin therapy within 1 year after T2DM diagnosis to eliminate the risk of including patients with autoimmune components (that is, type 1 diabetes mellitus (T1DM) or latent autoimmune diabetes of adults (LADA)). Inclusion and exclusion criteria are depicted in Table 1.

**Table 1 T1:** Inclusion and exclusion criteria

**Inclusion criteria**	**Exclusion criteria**
Diagnosis of T2DM with insulin therapy for at least 3 months and an HbA1c of ≥7%; negative islet cell autoantibody testing will be required for patients that received insulin therapy within 1 year after T2DM diagnosis	Type I diabetes mellitus or latent autoimmune diabetes of adults (LADA)
Proof of at least one microvascular manifestation of diabetes (for example, nephropathy, retinopathy, neuropathy)	T2DM on diet and/or oral medication
Residual pancreatic function, which is the premise for autogenic glycemic control assessed by stimulated fasting C-peptide laboratory tests with a minimum of 1.5 ng/mL	Heart failure (NYHA III-IV)
	Pregnancy
BMI 26–35 kg/m^2^	Malignant disease in the past 5 years
Age 30 to 65 years	History of major abdominal operation
	Permanent glucocorticoid or other immunosuppressive therapy
	Pituitary disease/Morbus Addison
	Renal failure (glomerular filtration rate < 45 ml/min)
	Proof of any liver cirrhosis above grade A according to the Child-Pugh-classification
	Expected lack of compliance or inability to informed consent

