### Randomization

Randomization will be performed after assessment of the inclusion and exclusion criteria and informed consent of the patient to participate in the study. Randomization will be performed at a ratio of 1:1 for the two treatment groups, using an online randomization tool (http://www.randomizer.at) which enables block randomization and stratification for each center. Four hundred patients will be recruited according to the sample size calculation in order to prevent random error and achieve sufficient strength for hypothesis testing of the primary endpoint.

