#### Primary endpoint

The primary endpoint is the time from randomization to one of the composite events, including death from cardiovascular causes, non-fatal myocardial infarction, coronary artery bypass grafting, percutaneous coronary intervention, non-fatal stroke, amputation, and surgery for peripheral atherosclerotic artery disease during the follow-up of at least 8 years according to the Steno 2 study. End-organ damage is also specified according to the Steno2 study from Gaede *et al.*[31,32]. Together with the expected accrual period of 2 years, this amounts to a maximum follow-up period of 10 years. If none of the above events are observed within the follow-up period, the date of the last follow-up is censored.

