### Statistical methods

#### Sample size

The study, with seven components as used in the Steno 2 study [31,32], is designed to demonstrate the superiority of the experimental group to the control group with respect to the hazard ratio for a composite event. The Steno2 study was used to estimate the rate of cardiovascular events we have to expect after 8 years of medical therapy. A reduction of diabetes-associated morbidity from 20%, as reported in the Steno 2 study for intensified conservative T2DM treatment, to 10% for surgical treatment will be defined as success and used for sample size calculation. Let *p*_S_ and *p*_C_ denote the cumulative incidence of one or more components of the composite endpoint for RYGB and standardized medical treatment, respectively. For exponentially distributed event times, event rates of *p*_S_ = 0.10 and *p*_C_ = 0.20 after 8 years correspond to a hazard ratio of 0.472 in favor of surgical treatment [31]. At the two-sided significance level of *α* = 5%, a total number of 56 events is required to detect this effect with a power of 80%. Assuming again exponentially distributed event times, an accrual period of 2 years and a minimal follow-up time of 8 years, the required number of patients to achieve this number of events is given by 336 in total, that is, 168 patients per treatment arm. Assuming a loss to follow-up rate of 20%, 200 patients should be randomly assigned to each intervention group (400 in total). This ensures sufficient power for the intention to treat analysis (ITT) and the complete cases per protocol (PP) analysis.

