#### Analysis of the primary endpoint

Each patient’s allocation to the different analysis populations (full analysis set according to the ITT principle, PP analysis set, safety analysis set) will be defined prior to the analysis. The allocation will be documented in the statistical analysis plan prior to database closure. During the data review, deviations from the protocol will be classified as minor or major. Major deviations from the protocol will lead to the exclusion of a patient from the PP analysis set.

The primary analysis will be performed using a Cox proportional hazards regression (*α* = 5%, two-sided) with covariates treatment group, age, duration of T2DM, and a stratification for each center. Confirmatory analysis will be based on the ITT population, with ICA-r imputation for missing values [33].

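### The confirmatory Cox model leaves out prior macrovascular disease although eligibility mixes patients with and without it; secondarily, procedures already scheduled at randomization count as primary events

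*Protocol article*

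**What the plan says.** **Eligibility.** Table 1 (Patient selection criteria) requires a microvascular manifestation of diabetes. Its one cardiac or vascular exclusion is "Heart failure (NYHA III-IV"). A past macrovascular event neither qualifies nor disqualifies a patient, and a vascular procedure already planned is not mentioned. The Discussion explains that the criteria follow the Steno 2 study so as to obtain a population at high macrovascular risk.

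**Randomization.** The allocation is 1:1 with an online tool "which enables block randomization and stratification for each center". No other stratification factor is named.

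**Model.** Analysis of the primary endpoint specifies a Cox regression "with covariates treatment group, age, duration of T2DM, and a stratification for each center". Under Safety measures, baseline values are compared between arms descriptively.

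**Endpoint.** Time runs from randomization to the first of seven components. Besides cardiovascular death and non-fatal infarction these are "coronary artery bypass grafting, percutaneous coronary intervention, non-fatal stroke, amputation, and surgery for peripheral atherosclerotic artery disease". Four of the seven are procedures. The Primary endpoint section makes no exception for a procedure already arranged at randomization.

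**Size.** The 8-year rates of 20% and 10% "after 8 years correspond to a hazard ratio of 0.472 in favor of surgical treatment" once set in the form "a total number of 56 events is required to detect this effect with a power of 80"%, which leads to 336 patients before the allowance for loss and 400 after it.

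**The concern.** The covariate list has been decided: two baseline characteristics plus center. Given that choice, the characteristic closest to the endpoint, namely whether the patient has already had one of its component events, is absent from both the strata and the model. With a target of 56 events there is little information to spare, and a prognostic covariate is a cheap way to recover some of it and to protect the estimate against an unlucky split between arms.

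The second, smaller matter is the event count. A procedure indicated and arranged before randomization, but carried out afterwards, meets the endpoint definition as written. Neither treatment could have prevented it, so it adds events with an expected hazard ratio of 1 and pulls the overall estimate towards 1.

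**Working it through.** **1. The plan's own figure.** Inputs from the Sample size section: 8-year rates 20% and 10%, two-sided 5%, power 80%, 2 years of accrual, at least 8 years of follow-up.

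- Hazard ratio: ln(0.90)/ln(0.80) = 0.472.
- Events (Schoenfeld): 4 × (1.960 + 0.842)² / (ln 0.472)² = 55.75, so 56.
- Mean event probability with exponential times and uniform accrual: 0.1668. Then 56/0.1668 = 335.7, so 336.

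Both figures reproduce. Nothing below changes them.

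**2. Power lost by omitting the covariate.** The documents give neither the share of patients with prior events nor its hazard ratio, so both are assumed: prevalence 20-30%, hazard ratio 2 to 4. The simulation had 168 patients per arm, marginal 8-year risks of 20% and 10%, censoring between 8 and 10 years, 2,000 runs per setting, and a Cox model with and without the history term. The gain from adding the term was about 0.4 to 4 points of power, larger when the assumed hazard ratio is larger. At a hazard ratio of 3, one set of runs gave 78.6% against 80.3% (prevalence 20%) and 77.3% against 79.7% (prevalence 30%). Age, diabetes duration and center were not simulated. If prior disease correlates with age or duration, the extra gain is smaller.

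**3. Chance imbalance, 200 per arm.** SD of the difference in prevalence = √(2p(1−p)/200).

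| Prevalence p | SD | 8 points in SDs | Probability of a difference above 8 points, either direction |
|---|---|---|---|
| 20% | 0.040 | 2.00 | 4.6% |
| 30% | 0.046 | 1.75 | 8.1% |

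Size of the shift at an assumed hazard ratio of 3, approximating each arm's mean hazard by 1 + 2p:

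- p = 20%, split 24% against 16%: ln(1.48/1.32) = 0.11.
- p = 30%, split 34% against 26%: ln(1.68/1.52) = 0.10.

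The simulated slope of 1.5-1.6 per unit of imbalance gives 0.12-0.13. The standard error of the log hazard ratio with 56 events is about 2/√56 = 0.27, so the shift is 0.37 to 0.48 of a standard error (0.10/0.27 to 0.13/0.27).

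**4. Scheduled procedures.** Let a share q of each arm have one, counted as an early event with hazard ratio 1, among 336 evaluable patients. The null events number 336q and the treatment-sensitive events (1−q) × 56.05. The average log hazard ratio is ln(0.472) weighted by the treatment-sensitive share. Power = Φ(|log HR| × √events / 2 − 1.96).

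| q (assumed) | Null events | All events | Average HR | Power |
|---|---|---|---|---|
| 0% | 0 | 56.05 | 0.47 | 80% |
| 1% | 3.4 | 58.9 | 0.49 | 77% |
| 2% | 6.7 | 61.7 | 0.51 | 75% |
| 5% | 16.8 | 70.1 | 0.57 | 67% |

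The documents give no value for q. The 5% row only shows how the loss grows.

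**The case against.** **Randomization already deals with prior disease.** This largely stands. Allocation at 1:1 balances it in expectation, the test stays valid, and the confidence interval allows for chance imbalance. A reader might infer that leaving the factor out biases the treatment effect. The documents do not support that, and a small simulation (60 runs per setting, too few to measure power or error rates) gave nearly the same average hazard ratios with and without the term: 0.49 against 0.49, 0.45 against 0.45, and 1.03 against 1.02 under no effect.

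**Past events are not outcomes.** Correct. A reader might infer from the open eligibility that earlier stents, strokes or amputations enter the endpoint. They do not, because time starts at randomization. Only procedures planned before and performed after it are affected.

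**Mixed risk was intended.** Also correct: high macrovascular risk is a stated aim, and admitting these patients is not an error. That is a reason to use the risk information in the analysis, not a reason to leave it out.

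**Event rules may sit in the full protocol or an endpoint charter.** This is fair for scheduled procedures and is why that part is secondary. It does not reach the covariate list, which the article states outright.

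**The work-up could distort one arm.** The article describes a cardiological assessment under the experimental group, so a reader might infer that extra procedures would be triggered there. The documents do not say what assessment controls receive, nor that any procedure follows, so this is not claimed.

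**A third covariate is a preference.** In part. No stated figure is wrong. But the gain is obtained at almost no cost.

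**Conclusion.** The point holds as a modest improvement to a fixed covariate set. Omitting the history of primary-endpoint events does not bias the comparison. It forgoes about 0.4 to 4 points of power, and it leaves unadjusted an imbalance above 8 points that would occur in about 5-8% of trials and move the log hazard ratio by roughly 0.1, in either direction. These sizes rest on an assumed prevalence of 20-30% and an assumed hazard ratio of 2 to 4 (3 for the shift), with age, diabetes duration and center left out of the simulation.

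The scheduled-procedure gap is real on the text shown but secondary. Its cost, power of about 77% at 1% and 75% at 2%, depends entirely on assumed rates. The stated 56 events and 336 patients are unaffected by either part.

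**What to change.** **Main change.** In Analysis of the primary endpoint, add history of any primary-endpoint event at screening (yes/no) as a prespecified covariate in the confirmatory Cox model, beside age and diabetes duration. Cost: one CRF item and one more model parameter. Stratification and sample size stay as they are.

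**Secondary change.** Record at screening, before allocation, any revascularization, amputation or peripheral artery operation already scheduled. State in the Primary endpoint section that a procedure so recorded does not count as a primary event. Cost: one further CRF item, one sentence, and possibly a few fewer counted events. Recording before allocation matters because the trial is open: deciding afterwards which procedures had been planned would bring a judgment made with knowledge of the arm into the primary endpoint.

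Both changes should be made before outcome data by arm are seen, since a later change could look data-driven.

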### Recruitment and timelines

Patients will be recruited by the Study Center of the German Surgical Society (SDGC) at the University of Heidelberg, Department of General, Visceral and Transplant Surgery in cooperation with the Department of Medicine I (Endocrinology) and Clinical Chemistry of the University of Heidelberg and correspondingly at the participating centers. Recruitment is planned to last 12 months. The first patient in to last patient out will be 120 months, and the proposed duration of the entire trial is 132 months.

### Randomization

Randomization will be performed after assessment of the inclusion and exclusion criteria and informed consent of the patient to participate in the study. Randomization will be performed at a ratio of 1:1 for the two treatment groups, using an online randomization tool (http://www.randomizer.at) which enables block randomization and stratification for each center. Four hundred patients will be recruited according to the sample size calculation in order to prevent random error and achieve sufficient strength for hypothesis testing of the primary endpoint.

### Interventions

#### Experimental group

A laparoscopic RYGB will be performed no later than 2 months after allocation to the experimental group. As part of the standardized preoperative assessment, a gastroscopy, laboratory tests, ultrasound of the abdomen, cardiological and endocrinological assessment will be performed.

The operation technique is as follows: The patient is positioned in the supine position 30° (reverse Trendelenburg) after a regular fasting time of 12 h. A single-shot of antibiotic prophylaxis is given (according to local standards of participating centers). Then a 15 mmHg pneumoperitoneum through the left upper abdomen is created. Next, five trocars are placed in the upper abdomen. The liver retractor is then positioned in the right upper abdomen. Initially, the gastroesophageal junction is identified. Then the stomach is transsected by the use of linear staplers to build a pouch of 4–6 cm height and 14–16 mm width. The omentum majus can be transected depending on the individual anatomy. At 70 cm from the ligament of Treitz, an end-to-side gastroenterostomy is performed using either a linear or circular stapler. To reconstruct the passage, a side-to-side jejuno-jejunostomy 150 cm from the gastrojejunostomy is performed (Figure 1). The proximal anastomosis is then checked for leaks by methylene blue.

**Figure 1 F1:**
[figure not shown]
Visualization of the gastric bypass post surgery.

After the operation, patients are hospitalized for approximately 5 days. Diabetic and hypertensive medication are paused and re-administered if needed according to the endocrinologist’s decision. After dismissal, standardized medical therapy of T2DM is administered according to the latest S3 Guidelines of the German Diabetes Association [8,9].

